#### Mediator analysis

We will conduct mediator analysis to investigate potential mechanisms of change following the intervention. Specifically, we will examine if improvements in parental scaffolding, sensitivity, and reciprocity mediates improvements in child language, joint attention, and EF at post interventions and follow-ups.

#### Moderator analysis

In addition, moderator analysis will be conducted to examine whether specific groups benefit more or less from the intervention. Specifically, we will investigate the associations between improvement status and participants’ characteristics, such as family socio-economic status, quality of home literacy environment, and parental intervention fidelity (e.g., number of sessions attended).

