### Intervention

#### Index group

The intervention was a group-based book sharing program for caregivers, “the Mikhulu Trust book sharing programme for children aged 10–24 months” (www.mikhulutrust.org). The program structure and content has been informed by the original Whitehurst model [39, 40]. The program has previously been evaluated with children aged 14–18 months [37, 39, 40]. It was adapted for the targeted age-group by selecting age-appropriate picture-books and by focusing on teaching caregivers’ book sharing techniques most relevant for when sharing books with infants. The intervention program was delivered by a trained facilitator weekly for five consecutive weeks to groups of around 4–6 parent-child dyads. Each session (60 min) was organized around specific topics and incremental techniques; see Table 1 for a description of the content for each session. During each session, the caregivers sat in a semicircle facing the facilitator. Sessions 2 to 5 began with a review wherein the participating caregivers shared and discussed their experiences of book sharing in the preceding week, with the guidance of the facilitator. In each session, key learning points were presented to caregivers through PowerPoint slides. The slides included instructive pictures and video clips to demonstrate the key techniques to apply during book sharing with their child. The caregivers were encouraged to be involved in the session by expressing their opinions and by asking questions about the session content. During this part of the session, toys were available on the floor for the children to explore.

**Table 1 Tab1:** Intervention sessions

Session	Session content
1	**Introduction and getting started** (using “Vi går på Babyrytmik” by Moa Eriksson Sandberg & Erik Sandberg). The benefits of book sharing to children’s development are presented. The key principles of book sharing are introduced and the caregiver is encouraged to engage the child actively with the book, to facilitate the child’s handling of the book, to help the child to turn pages and steady the book, to follow the child’s cues and interest, to praise the child, to have fun together, and to support their child. The importance of establishing a book sharing routine is emphasized.

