***Moderators***							
Parental socio-economic status	Parental level of education	Parent report	x				
Home literacy environment	Reading habits	Parent report	x		x	x	x
Parental intervention compliance	Attendance record, intervention dose (amount of practice), intervention experience	Facilitator/parent report		x			

*Abbreviations*: *EEG* Electroencephalography, *CDI* Communication Development Inventory, *ESCS* Early Social Communication Scale, *EEFQ* Early Executive Functions Questionnaire, *ECITT* the Early Childhood Inhibitory Touchscreen Task, *BSSI* the Book Sharing Scale for Infants

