### Potential moderators

The following variables will be used as potential moderators: *family socio-economic status* (indexed at baseline by parental report on highest parental education level: elementary school, high school, university < 3 years, or university >3 years ), *home literacy environment* (indexed by parental report on reading habits at all four assessments, e.g., frequency of reading for the child: never, 1–2 times per month, 1–2 times per week, or everyday/almost every day), and *parental intervention compliance* (indexed by intervention sessions attendance records, and self-reported practice of shared-reading between session, reported as days per week and minutes per day, and intervention experience, e.g., whether they think the book sharing training has been beneficial to them).

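### The moderator analysis asks who benefits more from the intervention but specifies an association with improvement, which cannot separate predictors of development from modifiers of the effect, and it does not restrict moderators to baseline values

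*Protocol article*

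**What the plan says.** The Moderator analysis section states its aim: "moderator analysis will be conducted to examine whether specific groups benefit more or less from the intervention". The next sentence fixes the method: "Specifically, we will investigate the associations between improvement status and" participant characteristics. The characteristics named are family socio-economic status, "quality of home literacy environment, and parental intervention fidelity (e.g., number of sessions attended"). Improvement status is not defined.

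The Potential moderators section and Table 2 say how these are measured:

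- Socio-economic status is parental education, taken at baseline.
- Home literacy environment is "indexed by parental report on reading habits at all four assessments".
- Compliance is described in Table 2 as "Attendance record, intervention dose (amount of practice), intervention experience", recorded during the intervention. Potential moderators adds "self-reported practice of shared-reading between session, reported as days per week and minutes per day". Its example of intervention experience asks whether the book sharing training was of benefit to the parent.

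The Statistical methods section names linear mixed models or analysis of covariance, adjusted for baseline scores, for intervention effects. Neither that section nor any other mentions an interaction between arm and a characteristic.

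**The concern.** Whether a group benefits more is a question about the difference between arms, and whether that difference changes across levels of a characteristic. An association between improvement and a characteristic answers another question: which children develop faster. Infants change quickly between 10 and 24 months in either arm, so anything that predicts the pace of development will be associated with improvement, whether or not it alters what the intervention does.

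The article gives its own reason to expect this. Its Background treats the quality of the home learning environment as a driver of language and cognitive development and links richer homes to better learning paths. Home literacy, one of the three listed moderators, is therefore a predictor of improvement on the authors' own account.

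The second problem is timing. Three of the four reading-habit measurements follow an intervention that acts on reading habits. In session 1 of the index programme, "The importance of establishing a book sharing routine is emphasized", and parents are asked to practise at home daily. A reading habit recorded after that may be a result of the intervention rather than a trait that marks out a subgroup. Attendance, practice and experience are all post-randomisation.

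At stake is a published statement that certain families gain more from the programme, which the analysis as written could not support.

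**Working it through.** **The plan's own figure.** The article gives no number for the moderator analysis. Its only calculation is 55 dyads per arm for d = 0.54, 80% power and two-sided 5%. The normal approximation gives 2 × (1.960 + 0.842)² / 0.54² = 15.70 / 0.2916 = 53.8, so 54. The t-based calculation gives 54.8, so 55. The figure reproduces and this point does not affect it.

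**Inputs for the check.**

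- From the article: N = 109 at post-assessment (Recruitment), d = 0.54 (Sample size), two-sided 5% (Statistical methods).
- Assumed: a 55/54 split, because the article gives only the total at that visit; and a correlation ρ between characteristic and improvement of 0 to 0.4, because the article gives none.

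**Model.** Improvement = d × arm + ρ × x + √(1 − ρ²) × e, with x and e independent standard normal. There is no arm-by-x term, so every moderator declared is false. Each setting had 4,000 simulated trials. The Monte Carlo standard error is √(0.05 × 0.95 / 4000) = 0.3 percentage points at a 5% rate and at most 0.8 points elsewhere.

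Because improvement status is undefined, three readings of the stated method were run beside the interaction test. Rejection rates at d = 0.54:

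| Assumed ρ | Pooled association | Index arm only | Improver by median split | Arm-by-x interaction |
|---|---|---|---|---|
| 0 | 5.0% | 5.0% | 4.8% | 5.0% |
| 0.1 | 18.0% | 11.4% | 12.7% | 4.5% |
| 0.2 | 52.8% | 30.7% | 36.1% | 5.1% |
| 0.3 | 86.5% | 62.5% | 67.4% | 4.7% |
| 0.4 | 98.8% | 86.2% | 92.1% | 5.0% |

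With d = 0 the pooled rates are 4.9%, 18.2%, 56.1%, 88.9% and 99.3%. Apparent moderators therefore arise equally often when the programme does nothing.

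**Hand check of the pooled column.** By Fisher's z, power ≈ Φ(atanh(ρ) × √(109 − 3) − 1.96). For ρ = 0.2: 0.2027 × 10.296 − 1.96 = 0.127, giving 55%. For 0.3: 0.3095 × 10.296 − 1.96 = 1.227, giving 89%. For 0.4: 0.4236 × 10.296 − 1.96 = 2.40, giving 99%. These agree with the simulation.

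**Reading habits measured after the intervention.** Suppose the arm shifts reading habits by 0.5 or 1.0 SD (assumed) and reading habits have no effect on improvement. The pooled association is then significant in 11% or 22% of trials, simply because both variables differ by arm. If an unmeasured cause also loads 0.3 to 0.5 on both (assumed), the range is 34% to 95%. The interaction test stayed at 4% to 5% here too. The reason to keep later reading habits out of an interaction model is thus one of meaning: a variable that the intervention moves does not define a subgroup that existed before it.

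**Power of the correct test.** For a 50/50 binary moderator with SD 1, four cells of 109 / 4 = 27.25 give SE = √(4 / 27.25) = 0.383. For an interaction of 0.54, Φ(0.54 / 0.383 − 1.96) = Φ(−0.55) = 29%. For 1.08, Φ(0.86) = 80%.

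**The case against.** The strongest defence is that a moderator analysis ordinarily means an interaction, that the sentence on associations is loose prose, and that the model belongs in a full protocol or analysis plan not shown here. This would succeed if the article had stopped at the aim. It goes on to specify a contrast, and that contrast does not answer the aim. A plan that followed the text would carry the error forward.

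Other parts of the defence stand, and they limit the point:

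- A reader might infer that the analysis is bound to mislabel predictors as moderators. It is not. At ρ = 0 the rate is 5%, and the index-only and median-split readings give less than the pooled one. Both are still inflated whenever the characteristic is prognostic (31% and 36% at ρ = 0.2).
- A reader might infer that home literacy is not a baseline variable. It is measured at baseline as well as later. The article does not say which visit's value enters the analysis; the fault is that it does not restrict it to baseline.
- A reader might infer that compliance exists only in the index arm. Attendance was recorded in the control arm too (Active control group), and nothing says that control parents were not asked about reading practice. Only the experience example is tied to the book sharing training.
- A reader might infer that adjusting for later reading habits biases arm comparisons within strata. The section describes no such comparison.

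None of the four hypotheses concerns moderation, and the section is presented as additional, so the trial's main comparisons are untouched.

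**Conclusion.** The point holds as a mismatch between a stated aim and a stated method, with moderator timing left open as a second fault. As written, the analysis can present a predictor of development as a modifier of the intervention effect. The false-moderator rate runs from 5% with no correlation to 99% at 0.4 on the pooled reading, and from 5% to 86–92% on the other two, against about 5% for an interaction test. These rates rest on the assumed correlations, the near-even split and a linear model with normal errors. The direction does not depend on them: any non-zero association with development in both arms inflates the rate.

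Parental education and baseline reading habits are sound choices of moderator; for them only the missing arm contrast is at fault. The sample size and the primary and secondary treatment comparisons are not affected.

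**What to change.** Reword the Moderator analysis section in three parts.

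1. Add an arm-by-moderator term to the baseline-adjusted analysis of covariance or mixed model already planned, on the continuous outcome rather than improvement status. Use baseline parental education and T1 reading habits only. Report each interaction estimate with its confidence interval and label the analysis exploratory.
2. Treat reading habits at T2 to T4 as outcomes.
3. Take attendance, practice and experience out of the moderator list and report them as a separate dose-response analysis, labelled non-randomised.

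All the variables are already collected, and the 24-month follow-up was still running when the article was written, so the cost is wording. The drawback is power: about 29% for an interaction as large as the planned main effect (0.54 SD) with an even binary split. An interaction of about twice that size (1.08 SD) is needed for 80%. A non-significant interaction should therefore not be read as showing that all groups benefit equally.

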### Dissemination plans

We will disseminate the study findings in several ways. We will publish them in highly ranked international peer-reviewed journals. Results will also be orally presented at international conferences on child development, psychology, and education. We will communicate our results to the wider public via local and national media, by using social media (Facebook and Twitter) and by posting summaries of the study at Uppsala Child and Baby Lab University webpage.

## Discussion

The REaL trial is an evaluation of a book sharing intervention for caregivers and their 10-month-old children. The intervention is conducted over 5 weeks and is designed to evaluate intervention effects on child language, joint attention, and EF. Its impact on parental behaviors (cognitive scaffolding, sensitivity, and reciprocity) will also be assessed. The trial includes long-term follow-ups and will therefore be able to clarify the durability of the intervention effects and potential spill-over effects. The intervention is relatively brief and involves modest levels of training. Thus, demonstrations of positive intervention effects on child and parental outcomes would be of significance for the development of early interventions to promote child development.

## Trial status

Recruitment to the trial began in January 2020. Due to the COVID-19 pandemic, recruitment paused between February 18 to May 15, 2020, and between October 21, 2020, and July 7, 2021. At the point of submitting this manuscript to the journal (17 March 2021), 97 out of the final 115 participants in the sample had been recruited. Recruitment to the study ended 5 August 2021. This paper represents version 1 of the protocol.

## Data Availability

Authorship will be granted for substantive contribution to the design, conduct, interpretation, and reporting of the trial. Publications will be made open access. Datasets generated during the current study will be deposited in publicly available repositories (where available and appropriate) 1 year after the completion of the study.

## Abbreviations

BSSI: Book Sharing Scale for Infants
CDI: Communication Development Inventory
ECITT: Early Childhood Inhibitory Touchscreen Task
EEG: Electroencephalography
EEFQ: Early Executive Functions Questionnaire
EF: Executive function
ESCS: Early Social Communications Scales
RCT: Randomized controlled trial
REaL: Roadmap to Executive functions and Language
